### Study design

The proposed study is a single-center, parallel group randomized controlled trial with pre-intervention, post-intervention, retention, and follow-up tests to determine the relative efficacy of the interventions: treadmill-based C-Mill therapy and the overground FALLS program. After giving informed consent, participants will be randomly assigned to one of the two interventions using an automated, custom-made minimization algorithm written in MATLAB. The minimization procedure is based on time after stroke, age and Functional Ambulation Category score to balance groups for these stratification factors. The research assistant will enter the data for randomization in the algorithm and the participant will subsequently be informed about the resulting group allocation before the pre-intervention tests. Subsequently, the assessor will schedule the participants for the assigned 5 week intervention program. Pre-intervention tests (T0) to characterize groups and obtain baseline values of primary and secondary outcome measures will be performed one week prior to the intervention program. Within one week after completing the intervention, post-intervention tests (T1) will be performed. The same tests will be conducted 5 weeks (retention tests, T2) and 12 months (follow-up tests, T3) after completing the intervention. All assessments will be performed at the rehabilitation center. Because of the nature of the intervention studied, therapists and participants cannot be blinded to group allocation. The assessor will also not be blinded to group allocation, because of pragmatic constraints related to the planning of assessments and therapy sessions. Figure 2 shows a flow chart of the procedures that participants will undergo at T0, T1, T2 and T3.

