### Data analysis

Descriptive group statistics will be used to characterize the two intervention groups in terms of sex, age, height, body mass, Mini-Mental State Examination, Functional Ambulation Category, medication use, co-morbidities, side and location of the lesion, current living situation, daily functioning and the use of assistive devices, as well as perceived discomforts during and after therapy sessions and participant’s experience with the therapy. An independent *t* test will be used to compare the mean number of steps taken per session between the two interventions.

Primary and secondary longitudinal outcome measures that are normally distributed will be analyzed using repeated-measures ANOVA with the between-subject factor group (two levels: C-Mill therapy and the FALLS program) and the within-subject factor time (four levels: pre-intervention [T0], post-intervention [T1], retention [T2], and follow-up [T3] tests). Post-hoc analysis using independent *t* tests between groups per time level will be performed in case of significant interaction effects. For ordinal or non-normal distributed variables, we will use Mann–Whitney *U* tests and Friedman tests to evaluate possible main effects of group and time, respectively. To analyze possible interactions between groups and times, we will apply Kruskal–Wallis tests to change scores (i.e., relative to the previous time level) at T1, T2, and T3. When significant, Mann–Whitney *U* post-hoc tests will be performed to identify between-group differences in change scores per time level. Significant effects are assumed for *P* < 0.05. Data will be analyzed as randomized. Missing data will be imputed using the data from the last available measurement.

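### Carrying the last value forward is the only missing-data rule, so the group comparison depends on how much dropout occurs, when, and in which arm

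*Protocol article*

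**What the plan says.** The Data analysis section of the protocol article gives one rule for every outcome and visit: "Missing data will be imputed using the data from the last available measurement". The sentence before it reads "Data will be analyzed as randomized". No assumption about why data go missing is stated, and no second method is set beside the rule.

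The filled-in data feed two kinds of analysis:
- Normally distributed outcomes, including the primary one if it qualifies, "will be analyzed using repeated-measures ANOVA with the between-subject factor group" and a four-level time factor (T0 to T3). Post-hoc t tests "between groups per time level will be performed in case of significant interaction effects".
- Ordinal or non-normal outcomes are tested for interaction by applying Kruskal–Wallis "tests to change scores (i.e., relative to the previous time level) at T1, T2, and T3".

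The Study design section gives the timing. T0 "will be performed one week prior to the intervention program", which lasts 5 weeks. "Within one week after completing the intervention, post-intervention tests (T1) will be performed". Then: "The same tests will be conducted 5 weeks (retention tests, T2) and 12 months (follow-up tests, T3) after completing the intervention". The Sample size section allows for 10–25% dropout by raising 14 per group to 20.

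**The concern.** Carry-forward makes a factual claim about each missing value: nothing has changed since the last visit. That claim sits badly with this trial. Both programs are described as promising for improving walking speed, yet someone who leaves before T1 is recorded as not improving at all. T3 exists to show whether gains last, yet someone who leaves after T1 is recorded as having kept the whole gain for about a year.

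The rule also matters more here than in many plans. Repeated-measures ANOVA in its classical form needs a complete row for each participant, so carried values decide what enters the primary analysis for everyone with a gap. For the change-score tests, each carried visit contributes a change of exactly zero. With 40 participants and up to a quarter expected to drop out, the estimated difference can come to reflect the pattern of dropout as well as the effect of therapy.

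**Working it through.** **Inputs from the Sample size section:** difference 0.50 km/h, SD 0.47 km/h, two-sided α 0.05, power 80%, dropout 10–25%, 20 per arm.

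**The plan's own figure.** n = 2 × 0.47² × (1.960 + 0.842)² / 0.50² = 13.87, so 14 per group, as stated. Allowing for dropout, 14/0.90 = 15.6, so 16, and 14/0.75 = 18.7, so 19. Twenty per group covers the stated range if dropouts only reduce the number observed.

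**Assumptions not in the documents.** The SD of 0.47 applies to the change from T0 to T1. Dropout occurs before T1 and is unrelated to outcome. The FALLS mean gain m is varied from 0 to 0.5 km/h. The test is a t test on change at T1, with power and type I error found by simulation.

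**Equal dropout d in both arms.** A carried T0 gives a change of 0, so an arm with true mean gain μ has
- mean (1 − d)μ
- variance (1 − d) × 0.47² + d(1 − d)μ²

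The difference becomes (1 − d) × 0.50, that is 0.90 × 0.50 = 0.45 or 0.75 × 0.50 = 0.375 km/h. The second variance term grows with μ, so power also depends on m.

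| Dropout before T1, both arms | Estimated difference (true 0.50) | Power with carry-forward, m = 0.3 | Range for m = 0.5 to 0 | Power, observed data only |
|---|---|---|---|---|
| 10% | 0.45 | about 82% | about 78–86% | about 87% (18 per arm) |
| 25% | 0.375 | about 66% | about 58–77% | about 80% (15 per arm) |

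**Unequal dropout, no true difference.** If both arms gain g, the spurious difference is g × (0.25 − 0.10) for dropout of 10% versus 25%.
- g = 0.3: 0.3 × 0.15 = 0.045 km/h, type I error about 6%
- g = 0.5: 0.5 × 0.15 = 0.075 km/h, type I error about 8%

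The sign follows whichever arm loses more. Observed-data tests stay near 5%. With equal dropout, carry-forward also stays near 5%.

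**Loss after T1.** Suppose the true difference is 0.50 km/h at T1 and has faded to 0 at T3. Carrying T1 forward for a share d gives d × 0.50 at T3: 0.05 km/h at 10% and 0.125 km/h at 25%. Here the error inflates the difference.

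**Length of carry.** T1 to T3 is about 12 months. T0 to T3 is one week, plus 5 weeks of program, plus 12 months, so more than 13 months.

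**The case against.** The strongest reply is that serious harm needs high early dropout or marked imbalance, and the documents establish neither. The 10–25% range comes without timing, and much of the loss could fall between T2 and T3. At 10% early dropout and a FALLS gain of 0.3 km/h, power is still about 82%. Duration, frequency and therapist attention are matched, and nothing in the article predicts that one arm will lose more. All of this stands, and it is why the figures are given as ranges.

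The calculation is also a T1 change-score test, not the planned two-by-four ANOVA. The power of that interaction depends on the course to T3 and on within-person correlation, which are not given. That stands too: the figures show the mechanism and its order of size, not this trial's power.

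A reader might infer three stronger claims that the material does not support:
- **Carry-forward always dilutes the effect.** It does so for similar dropout before T1. With unequal dropout, or loss after T1 with fading effects, it can inflate the difference.
- **Single imputation necessarily gives wrong standard errors and too many false positives here.** In the T1 setting with equal dropout, type I error stays near 5%. The excess comes from imbalance.
- **The margin of 20 per arm is lost throughout the dropout range.** For a FALLS gain of 0.3 km/h, the shortfall below 80% appears toward the upper end only.

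The reply that such detail belongs in a fuller protocol or analysis plan does not help. The article states this rule; it does not leave it open.

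**Conclusion.** The concern holds in this form: the sole missing-data rule assumes no change after the last visit, so the estimated group difference depends on the amount, timing and balance of dropout, and its bias has no predictable direction. It therefore cannot be defended as conservative.

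The shrinkage of the estimate by 10–25% at T1 follows directly from the plan's own dropout range, given equal dropout before T1 that is unrelated to outcome. The loss of power and the excess type I error rest further on the assumed gains. Both are modest at the favorable end and material at the other: power is about 58–77% at 25% early dropout, and type I error about 6–8% at 10% versus 25%. Where most loss falls after T1, the question shifts to T3, where retention of benefit would be partly assumed instead of measured.

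**What to change.** For the primary outcome and other normally distributed outcomes, replace both carry-forward and the complete-row ANOVA with a likelihood-based mixed model for repeated measures. It should use every observed value of all randomized participants, with T0 as a covariate or constrained baseline, group by time, and an unstructured covariance. It is valid if data are missing at random given what was observed, and the plan should state that assumption.

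For ordinal or non-normal outcomes, which would otherwise be left without a rule, test observed change scores or use multiple imputation, without carry-forward. With perhaps 15 completers per arm, keep any imputation model simple.

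Carry-forward may stay as a labelled sensitivity analysis.

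Cost: the primary model changes, so this is more than a one-sentence edit, and there is a little more analysis work. No new data are needed, and the analysis as randomized is kept. The change does not rescue everyone: allocation comes before T0, and a participant who leaves with no measurement at all contributes no outcome information under either approach.

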## Discussion

This randomized controlled trial will evaluate the relative effects of treadmill-based C-Mill therapy and the overground FALLS program on walking speed and walking adaptability in people with stroke. Although both C-Mill therapy and the FALLS program incorporate practice of walking adaptability and thereby aim at improving community ambulation, and first results are encouraging in this regard [9, 14, 15], it is hypothesized that C-Mill therapy will result in better outcomes than the FALLS program, as a result of the expected greater amount of walking practice owing to treadmill training [18, 20–22]. The results of the study of Moore *et al.* [19] indeed showed significant gains in daily stepping and walking efficacy after treadmill training, compared with conventional physical therapy, which appears to be related to the number of steps taken per session. In this study, we will explicitly test the anticipated greater amount of walking practice with treadmill training by comparing the registered number of steps taken per session between the two intervention groups.

The expected superior outcome of C-Mill therapy relative to the FALLS program may be further mediated by the possibility of tailoring the training to the patient’s needs and progress. During C-Mill therapy, the therapist can adjust the difficulty of the different exercises by manipulating content parameters, such as the variation in the sequence of stepping targets, the obstacle size and available response time for obstacle negotiation, and the degree of acceleration and deceleration of the moving walking area. As progressive training has superior effects [29–31], this patient-tailored challenge of C-Mill therapy might be beneficial, compared with the FALLS program. Conversely, the use of real obstacles and context and the practice of falling techniques might favor outcomes of the FALLS program compared with C-Mill therapy for its superior context-specificity.

A methodological strength of this study is that both interventions will be matched for therapy duration, frequency, and therapist attention. This means that if there is a superior effect on walking adaptability and walking speed of one of the interventions, this will be realized by the same investment in time and resources. Furthermore, both interventions implicitly utilize and train the direct visuolocomotor control of walking in an enriched environmental context [52, 53], allowing for a direct and natural visuolocomotor control in which the point of gaze is typically coupled to future foot placement locations. The two interventions in this study are similar with regard to visuolocomotor control of step adjustments relative to environmental context (e.g., real obstacles in the FALLS program, real visual obstacles in C-Mill therapy). The proposed trial of Hollands *et al.* [54] also testifies to the growing interest in the use of visual cues for task-specific gait training, thereby also implicitly training visuolocomotor control [54]. Hollands *et al.* intend to compare usual care without visual cues to overground visual cue training and treadmill visual cue training (using the C-Mill) in persons with stroke to examine the feasibility of task-specific locomotor practice incorporating visual cues. Therefore, our study, in combination with the study of Hollands *et al.* [54], might underpin the importance of visuolocomotor control in gait rehabilitation, as well as the potential surplus value of a treadmill in that regard.

A limitation of this study is that it involves only one center. This might influence the generalizability of the research results to other rehabilitation centers. Another limitation of this study is the non-blinding of the assessors. To reduce potential influence of this limitation on the outcomes, instructions will be standardized and tasks will be computerized when possible.

In summary, this study will shed light on the effects of treadmill-based C-Mill therapy compared with the overground FALLS program and thereby on the relative importance of the amount of walking practice as an important ingredient of effective interventions of walking speed and walking adaptability after stroke. Hence, the results of this study will be important in optimizing effective intervention programs directed at improving walking speed and walking adaptability after stroke.

### Trial status

Recruitment commenced in 2013 and is ongoing. Results of this study are expected in 2017.

## Abbreviation

ANOVA, analysis of variance; DTP, dual-task performance
